## Abstract

**Background:**

Developing health services is a key strategy for improving the community health provided by public health nurses. However, an effective educational program for improving their skills in planning such services has not been developed. To describe our program and its evaluation protocol for the education of middle-level public health nurses to improve their skills in developing new health services to fulfil community health needs in Japan.

**Methods:**

In this randomized control trial, eligible participants in Japan will be randomly allocated to an intervention group and a control wait-list group. We will provide 8 modules of web-based learning for public health nurses from July to October 2018. To ensure fairness of educational opportunity, the wait-list group will participate in the same program as the intervention group after collection of follow-up data of the intervention group. The primary outcomes will be evaluated using the scale of competency measurement of creativity for public health nurses at baseline, immediately after the intervention. Secondary outcomes will be knowledge and performance regarding program development of public health nurses.

**Discussion:**

This study will enable the analysis of the effects of the educational program on public health nurses for improving their competency to develop new health services for fulfilling community health needs and enriching health care systems.

**Trial registration:**

We registered our study protocol to the University hospital Medical Information Network- Clinical Trials Registry approved by International Committee of Medical Journal Editors (No. UMIN000032176, April, 2018).

## Background

Improving public health is a key to reducing inequalities and the social gradient. Public policy should be developed based on the social determinants of health, and public health care is also required to improve these social determinants [1]. Development, implementation and evaluation of policies and services assist in promoting the health, well-being, and equity of society. The concept of Health in All Policies builds capacity, systems, and resources in the community [2]. In many countries, public health nurses (PHNs) are responsible for promoting and improving community health [3]. Through their daily practices, PHNs identify health issues regarding individuals, families, and communities that require solving by the development of public health policies and services [4]. Filling the gap between community health needs and enriching community health care systems is an important population health management strategy of PHNs [5, 6].

Developing competency to create health services remains one of the most important challenges in public health nursing [7]. In the program planning field, tacit knowledge was found to play a big role, and knowledge translation was a key to developing innovative public health services [8]. We previously demonstrated that PHNs identified the difficulties of clients by focusing on unsolved community health needs. They utilized this evidence as the basis for program development [9]. However, many PHNs felt a lack of competency in planning health programs, and wanted to develop the skills required for it [10, 11]. To increase the capability and confidence of PHNs in planning health services, some educational programs have been conducted [12–15]. These programs chose face-to-face group sessions so PHNs could enrich their knowledge as well as exchange their experiences with each other. However, this educational style is limited regarding the number of participants, owing to time and location constraints.

### Study objectives and hypotheses

The aim of this study was to evaluate the following: (1) the effectiveness of the newly designed educational program for developing health service-planning skills of PHNs; and (2) identifying the PHNs that will benefit the most from participating in our educational program. In this report we show our research protocol and an overview of our educational program.

The PICO hypothesis of this study is as follows: (1) participants: middle-level PHNs who have worked in public administration; (2) intervention: providing an educational program regarding development of health services; (3) comparison: providing no program, and (4) outcome: improving the participants’ knowledge and performance of health service planning.

## Methods

### Study design and settings

This will be a single-blind and parallel group randomized controlled trial. PHNs will be randomized to either the intervention group or the control group [1:1]. After completing the intervention and collecting the follow-up data, the wait-list control group will have an opportunity to participate in the same educational program as the intervention group.

This study will consist of web-based learning modules and face-to-face group sessions. The study participants will take web-based learning modules at their time and place of choice within Japan. After that, PHNs who want to discuss with other participants about community health needs and how to solve it by developing a new health services will join a face-to-face group session that will be held in Sendai and Kobe, Japan.

### Participants

PHNs must meet the following inclusion criteria: (1) have worked on a full-time basis in public administration, and (2) have experience as a municipal or prefectural PHN of ≥5 years and ≤ 20 years [27]. The exclusion criterion is holding a position above the level of unit chief.

### Sampling, informed consent and randomization

In Japan, the number of PHNs who worked at prefectural or municipal governments in 2014 was 34,500, and one third of them were middle-level PHNs [28]. We will send 48 letters to the head PHNs of prefectural and 128 municipal main government offices in May 2018. We will ask each head PHN to share the information about this study with middle-level PHNs in their institution, and consequently, middle-level PHNs who are interested in this study are expected to access the study home page. Recruitment will be conducted from April to the end of June 2018. Only middle-level PHNs who read the explanation of this study and agree to join it and meet the inclusion criteria will be registered as study participants (Fig. 1). We provided web-based written information about the study, participation and publication of the results. Before study registration, we obtained web-based written informed consent from participants. All researchers will confirm the eligibility of PHNs.

**Fig. 1 Fig1:**
[figure not shown]
Consolidated Standards of Reporting Trial flow chart

All data were anonymized and do not include any personal information or the name of public administrations. We provided web-based written information about the study and obtained informed consent from participants before study registration. To protect the privacy of the participants, we will prohibit recording of the group sessions and will use nicknames for each participant.

Using a random number table, the statistician who was a co-researcher will allocate participants by equal computer-based randomization to the intervention group and the wait-list control group. To protect privacy, we will not obtain personal information and will not consider the size of each community and local government as adjustment factors. To minimize the difference in the number of participants between the two groups, we will use a permuted-block method.

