### Data collection

After registration of the eligible participants, we will collect individual data at baseline, immediately after the intervention. At baseline, all participants will fill in a web-based questionnaire including demographic information, such as age, gender, education level, position, population size of their municipality, number of residents per PHN in their municipality, their affiliation, previous experience in developing or participating in program development, existence of colleagues or bosses who actively work on program development, and daily practices that will help to build their skills in program planning. We will send the news letters for all participants to prevent drop out. This research was not harmful intervention, so we do not have data monitoring committee.

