#### Statistical analysis

Intention-to treat analysis will be utilized to assess the main effect of our intervention. We will calculate the initial drop-out rate as 30%, which will affect the sample size. Even if this rate exceeds 30%, we will not perform an additional recruitment of participants. We will compare the baseline characteristics of the intervention and control group using the *t*-test, and chi-square/Fisher exact test. In addition, ANOVA will be performed to identify factors affecting CMC, and knowledge and behavior regarding program development. To confirm significant improvements in competency, logistic regression analysis will be conducted. PHNs will also be analyzed in groups by years of experiences as PHNs, to identify the group that will benefit the most from participating in our educational program.

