This study has a few limitations. First, the drop-out rate will be high and the number of participants will be limited. Because it is common for PHNs to attended on-the-job training, which is based on an order from their boss as part of their work on weekdays in Japan. Our study is off the job training on weekends. Despite of sending letters of recruitment throughout Japan, the PHN who have high motivation will complete all modules. This will be a potential factor for selection bias in the present study.

Second, contamination of the intervention will occur in the control group. We will explain that sharing of the contents of the intervention among study participants is strictly prohibited. However, we will not be able to confirm whether the participants actually follow our instructions or not. Because of the protection of privacy, we will not collect the names of the communities in which the PHNs are working. Therefore, we will not be able to identify PHNs working in the same organization and put them into different educational group.

Despite of these limitations, this randomized controlled study will show the effects of an educational program aimed to improve the competency of middle-level PHNs to develop new health services for solving community health needs in Japan. Through collection of data over one year, we will confirm whether our user-friendly educational program will be useful for improving program planning competency of middle-level PHNs.

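### The privacy reason for not using community size as an adjustment factor conflicts with the baseline questionnaire, and the exclusion is not limited to allocation (minor)

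*Protocol article*

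**What the plan says.** The allocation paragraph under Sampling, informed consent and randomization (after the Fig. 1 caption) states that, for privacy reasons, the researchers will collect no personal information and "will not consider the size of each community and local government as adjustment factors". The next sentence gives the allocation method: "To minimize the difference in the number of participants between the two groups, we will use a permuted-block method". No stratification factor is named.

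The Data collection section lists the baseline questionnaire items for all participants. They include "population size of their municipality, number of residents per PHN in their municipality, their affiliation".

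The limitations in the Discussion say what is withheld for privacy: "we will not collect the names of the communities in which the PHNs are working". The text under Fig. 1 likewise says that the data are anonymized and leave out the names of administrations.

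The Statistical analysis section plans a comparison of baseline characteristics between arms and says that "ANOVA will be performed to identify factors affecting CMC, and knowledge and behavior regarding program development". It neither lists size among those factors nor excludes it. CMC itself is measured at baseline and immediately after the intervention (Abstract, Methods).

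**The concern.** A rule is given with a reason, and the document's own data collection defeats the reason. If municipality population size already sits in the dataset without a community name, using it in a model discloses nothing further.

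The scope of the rule is also open. The term adjustment factors is ordinary language for covariates in an outcome model as well as for allocation factors. An analyst who takes the sentence literally would leave size out of the CMC model. Another would take it as a remark on randomization and feel free to include size. That choice should not be left until the data have been seen.

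The stake is limited. A baseline variable related to CMC reduces residual variance when it is included and corrects for chance imbalance between arms. Leaving it out forgoes that gain.

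**Working it through.** **1. The passages side by side.**

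| Item | Randomization paragraph | Data collection | Discussion, limitations |
|---|---|---|---|
| Community size | Not considered, for privacy | Collected (municipality population size) | Not mentioned |
| Local-government size | Not considered, for privacy | Indirectly only (residents per nurse) | Not mentioned |
| Affiliation | Not mentioned | Collected | Not mentioned |
| Community name | Not mentioned | Not listed | Not collected, for privacy |

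Privacy is protected by withholding names. It does not account for excluding a size value that every participant supplies. The match is close for community size and only indirect for local-government size.

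**2. The plan's own figure.** Inputs from Sample size: effect size 0.50, 80% power, alpha 0.05, 134 analysed (67 per arm). The sidedness is not stated; two-sided is assumed.

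- Two-sided t-test: 63.77, so 64 per arm (128 in total).
- Two-sided Wilcoxon-Mann-Whitney test with a normal parent: 63.77 / (3/π) = 63.77 / 0.955 = 66.8, so 67 per arm (134 in total). This reproduces the stated number exactly.
- Power at 67 per arm: 80.1% by the Wilcoxon calculation, 81.9% by the t-test.

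The sample size assumes no covariate adjustment, so leaving size out does not make it wrong.

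**3. Possible gain from adjusting for size.** The documents give no R-squared, so 2%, 5% and 10% are assumed. Adjustment multiplies the residual variance by (1 − R²), so the effective standardised difference is d = 0.50 / √(1 − R²). Two-sided t-test, 67 per arm:

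| Assumed R² | d | Power |
|---|---|---|
| 0 | 0.500 | 81.9% |
| 0.02 | 0.505 | 82.7% |
| 0.05 | 0.513 | 83.8% |
| 0.10 | 0.527 | 85.7% |

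At R² = 0.10 the gain is equivalent to 134 / 0.9 = 149 analysed, or about 15 more participants. At R² = 0 there is no gain.

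**4. With baseline CMC in the model.** R² must then be read as incremental: the share of the remaining variance that size explains. The table holds if 0.50 is the standardised difference on that remaining scale. If 0.50 is instead the unadjusted effect size, baseline CMC has already raised power and size adds fewer points. For example, assume a correlation of 0.5 between baseline and post-intervention CMC. The residual variance is 0.75 and power is 91.3%. An incremental 2% gives d = 0.50 / √(0.75 × 0.98) = 0.583 and 91.8%. An incremental 10% gives d = 0.50 / √(0.75 × 0.90) = 0.609 and 93.8%.

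**5. Chance imbalance.** The standard deviation of a standardised baseline difference is √(2/67) = 0.173. An absolute difference above 0.25 corresponds to z = 0.25 / 0.173 = 1.45 and has probability of about 15%. An imbalance of exactly 0.25 shifts the unadjusted CMC difference by 0.25 × √R², which is 0.035 SD at R² = 0.02 and 0.079 SD at R² = 0.10, against a target of 0.50 SD.

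**The case against.** The best reply is that the sentence stands between the description of computer-based allocation and the permuted-block method, so it says only that size will not be an allocation factor. That is the most natural reading. Keeping workplace characteristics from the co-researcher who allocates also fits the blinding of researchers to personal information described under Minimizing bias. Unstratified permuted blocks are a valid method. All of this stands. What remains is that the sentence does not say it is limited to allocation, and that the reason it gives does not fit with collecting size.

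The reply also notes that prognostic value is assumed. That stands for any numerical association: none is given. The Background does link personnel downsizing with busy nurses and difficulty in planning services, which makes residents per nurse a plausible correlate, but no more than plausible.

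A reader might infer more than the text supports:

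- **That the data are discarded.** They are collected, and the planned baseline comparison and ANOVA could use them.
- **That affiliation is barred.** The sentence names only size.
- **That the aim of finding which nurses benefit most is weakened.** The Statistical analysis section pursues that aim by years of experience, and nothing in the sentence prevents other subgroup analyses.
- **That the effect estimate is biased.** Omitting a covariate or stratifier from a 1:1 randomized comparison does not bias it.
- **That the blocks should be stratified by size.** The article says "After registration of the eligible participants, we will collect individual data at baseline, immediately after the intervention", which does not place the questionnaire before allocation. Stratification would depend on that order and is in any case a matter of preference.

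**Conclusion.** The inconsistency is established from the text: size is refused for privacy, yet municipality population size is collected without names. The scope of the refusal is unclear, with allocation the likelier meaning.

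The consequence is small. Under the assumed incremental R-squared of 2% to 10%, adjusting for size adds about 1 to 4 power points to a starting value of about 82%, and less if baseline CMC has already raised the power. The gain could be nil. These figures rest on a two-sided t-test, 67 analysed per arm, an effect size of 0.50 and an R-squared that the documents do not supply. The gain is in precision and in correcting chance imbalance, not in removing bias, and the stated sample size is unaffected. Severity: minor.

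**What to change.** 1. In the randomization paragraph, state that the exclusion of community and local-government size applies to allocation only, or delete it. If it is kept, give a reason that is consistent with the Data collection section.
2. In the Statistical analysis section, prespecify a linear model for post-intervention CMC with allocated arm, baseline CMC and municipality population size as terms.

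The cost is a sentence in each place. No new data and no community names are needed, and the randomization is unchanged. The one practical burden is a rule for missing values of population size.

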### Sample size

We calculated that for an effect size of 0.50, 134 PHNs must be analyzed for the evaluation (intervention group: *n* = 67; control group: *n* = 67). This number is assuming a statistical power of 80% and an alpha value of 0.05 by using G*Power 3.1.9.2. [29, 30] We anticipated a drop-out rate of 30%, and hence concluded that 200 participants will be required.

### Minimizing bias

For minimizing bias, the researchers will be blinded regarding the personal information of the participants. The participants will enter their base-line data, follow-up data, and evaluation data of the educational program without involvement of the researchers. The participants will evaluate their competency regarding program planning using the web-based questionnaires that they will fill in by themselves. In addition, to prevent the exchange of information about the educational program between the intervention and the wait-list control group, we will explain the meaning of contamination to all participants in writing and on the homepage. We will send a URL address that can only be opened with a password, and which needs to be accessed for the training materials, to the e-mail addresses of the participants in the intervention group.

### Description of the intervention: Overview of the educational program and its learning objectives

In designing our 3-month educational program for PHNs to acquire skills in health service planning, aimed to solve community health needs identified through reflecting on their daily routine, we will take advantage of the large amount of experience of middle-level PHNs. This is based on previous studies [4, 9, 12, 14, 15, 23, 24], and the adult-learning theory [31] which showed that having a large amount of experience and reflecting on it will contribute to learning.

The main theme and objectives of each module are summarized in Table 1. After watching web-based learning modules 1–3, participants will fill out the worksheet to analyze the association between community health needs and its causes through reflecting on their daily practice. After watching web-based learning sessions 4–8, participants will write a proposal of a new health service based on community health needs that they identified.

**Table 1 Tab1:** Title of web-based learning modules, optional group session, and their objectives

	Title of module		Objectives
Web-based learning modules	1. Recall your great experiencing as a public health nurse	1	To understand the theoretical concept of program development, to efficiently solve the health issues of individuals and the community.
		2	To rediscover the role of PHNs through reflection of their own practice.
		3	To build motivation of participation.
	2. Finding time to think about program planning within your busy work schedule	1	To understand the necessity of maximizing the efficiency of their daily practices.
		2	To understand the needs of preventive intervention by PHNs.
	3. Identifying community health needs through analyzing the people who require a large amount of the time and help of PHNs	1	To clarify the health needs of the people who require a large amount of time and help from the PHNs.
		2	To analyze the causal relationships of the community health need.
	4. Organizing the evidences to confirm the necessity of program development	1	To understand the evidences to confirm the necessity of program development and how to collect such evidence.
	5. Developing a partnership with your colleagues and collaborators for promoting a program planning	1	To understand the key community stakeholders and collaborators of program planning.
		2	To share the community agenda and to build a consensus with the collaborators.
	6. Breaking the difficulty of obtaining budget	1	To understand the budget for developing a new program.
		2	To understand the necessity in cost-benefit-analysis of program planning.
	7. Common mistakes for analyzing a communith health need	1	To understand the common mistakes for analyzing a community health need.
	8. Common mistakes for developing a proposal of a new health program	1	To understand the common mistakes for developing a proposal of a new health program.
Optional group session	1. Identifying community health needs and developing a proposal of a new health program	1	Through face-to-face group sessions, participants will analyze and identify community health needs.
		2	Identifying the necessity of evidence which will support the existence of community health needs, and discuss about ways to fulfill them.
		3	Creating their proposal of a new health program: methods, expected effects, plan of evaluation indicators.

After watching 8 web-based modules, we will have an optional group session for the PHNs who want to discuss with other participants about community health needs and developing a proposal of a new health program. Each group will consist of 5 or 6 participants, to enable in-depth discussions. To decrease dropout rate, group session is an optional module.

After developing our educational program, we asked four middle-level PHNs and one professor who supervises PHNs working in prefectures and municipalities to check the contents of it as a pre-test. In accordance with their comments, we revised the explanation and confirmed that the contents of the program will cover the main skills of program planning that the PHNs should acquire.

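### Optional discussion groups of 5 or 6 may create clustering in the intervention arm only, which neither the sample size nor the named analyses allow for; any resulting error is small and anti-conservative

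*Protocol article*

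**What the plan says.** Protocol article, Study design and settings: "This study will consist of web-based learning modules and face-to-face group sessions". Nurses take the modules individually. Those who wish to can then join a session, held in Sendai and Kobe. The same section sets individual allocation: "PHNs will be randomized to either the intervention group or the control group [1:1".

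The text after Table 1 makes the session optional, as a way to limit dropout, and fixes the group size: "Each group will consist of 5 or 6 participants, to enable in-depth discussions". According to Table 1, attendees identify community needs, discuss ways to meet them and create proposals.

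The control arm receives no program until follow-up has been collected (Study objectives and hypotheses; Wait-list control group). Data collection takes place at baseline and directly after the intervention.

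Sample size: "We calculated that for an effect size of 0.50, 134 PHNs must be analyzed for the evaluation", that is 67 per arm. "This number is assuming a statistical power of 80% and an alpha value of 0.05 by using G*Power 3.1.9.2". Then: "We anticipated a drop-out rate of 30%, and hence concluded that 200 participants will be required". No design effect appears.

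Statistical analysis names intention-to-treat, then "ANOVA will be performed to identify factors affecting CMC, and knowledge and behavior regarding program development", and logistic regression to confirm improvement. No term for the session group is mentioned.

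**The concern.** The CMC and the 26 questions are self-ratings of the skills practised in the session. Nurses who have worked through the same discussion in a group of 5 or 6 may rate themselves more alike than nurses from different groups. Before follow-up, this can happen in the intervention arm only.

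Standard ANOVA and logistic regression take observations as independent, and the sample size does the same. With a positive within-group correlation, the variance of the intervention mean is larger than such an analysis reports. The confidence interval is then too narrow and the type I error exceeds 5%, which favours declaring the program effective.

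**Working it through.** **The plan's own figure.** For effect size 0.50, two-sided alpha 0.05 (sidedness is not stated) and 80% power, a t-test needs 64 per arm (128). The two-sided Wilcoxon-Mann-Whitney calculation gives 67 per arm (134), which is the stated number, with power 0.801. A t-test at 67 per arm has power 0.819. Each version assumes independent nurses. Dropout: 134/0.70 = 191.4, so 192; the plan rounds up to 200, which leaves 200 × 0.70 = 140 analysed, or 70 per arm.

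**Inputs not in the documents (assumed).** Attendance p among intervention nurses: 30% to 100%. ICC: 0.02 to 0.10. Mean group size m = 5.5, from the stated 5 or 6.

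**Formulas.** Each attendee shares a covariance of ICC × σ² with m − 1 others; everyone else is independent.

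- Intervention-arm design effect: DE = 1 + p(m − 1)ICC. Control arm: 1.
- True SE divided by reported SE: r = √[(1 + DE)/2]. Understatement: 1 − 1/r.
- Type I error: 2[1 − Φ(1.96/r)].
- Power with the SE corrected (normal approximation): Φ(0.50/√[(1 + DE)/n] − 1.96).

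**Example, p = 0.5 and ICC = 0.05.** DE = 1 + 0.5 × 4.5 × 0.05 = 1.1125. r = √(2.1125/2) = 1.028. Type I error = 2[1 − Φ(1.907)] = 5.7%. Power at 67 per arm = Φ(2.816 − 1.96) = 0.80.

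| Attendance | ICC | DE | r | SE understated | Type I error | Power, 67 per arm | Power, 70 per arm |
|---|---|---|---|---|---|---|---|
| none | – | 1.00 | 1.000 | 0% | 5.0% | 0.82 | 0.84 |
| 30% | 0.02 | 1.03 | 1.007 | 0.7% | 5.2% | 0.82 | 0.84 |
| 50% | 0.05 | 1.11 | 1.028 | 2.7% | 5.7% | 0.80 | 0.82 |
| 50% | 0.10 | 1.23 | 1.055 | 5.2% | 6.3% | 0.78 | 0.80 |
| 80% | 0.05 | 1.18 | 1.044 | 4.2% | 6.0% | 0.79 | 0.81 |
| 80% | 0.10 | 1.36 | 1.086 | 7.9% | 7.1% | 0.76 | 0.78 |
| 100% | 0.05 | 1.23 | 1.055 | 5.2% | 6.3% | 0.78 | 0.80 |
| 100% | 0.10 | 1.45 | 1.107 | 9.6% | 7.7% | 0.74 | 0.76 |

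The power columns are on the scale of a comparison of means. If the Wilcoxon calculation is the intended one, the margin is thinner. Going from 134 to 140 nurses then absorbs (1 + DE)/2 up to 140/134 = 1.045, so DE up to about 1.09, or p × ICC up to 0.09/4.5 = 0.02.

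**The case against.** The strongest objection is that the core teaching is individual. A reader who sees the group size might infer that intervention nurses are taught in groups and that the standard error is therefore certainly too small. The article does not support that. The session is a single add-on for those who want it. Recruitment is nationwide, the sessions are in two cities, and the Discussion describes the training as off the job and at weekends. Full attendance looks unlikely, and non-attendees remain independent. This stands: it moves the likely size towards the lower part of the range, without removing the effect among those who attend.

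The timing is also open. The Abstract describes what is provided as the eight web modules, and the session follows them. If follow-up precedes the session, the clustering does not reach the primary outcome. Study design and settings counts the sessions as part of the study, so measurement after them is the natural reading, but it is only a reading.

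A reader might also infer that the trial loses its stated 80% power. At the 140 nurses expected after dropout, the table shows that this happens clearly only with high attendance and ICC near 0.10.

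Finally, the article is condensed, and an error structure or a session code may sit in documents not shown. Nothing in the Statistical analysis section rules out a group term. That answers the modelling part if such text exists. It does not answer the Sample size section, which states its power with no mention of the independence behind it. Nor can any later analysis use group membership that was not captured at the session.

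**Conclusion.** The point holds conditionally. Three things must be true together: some intervention nurses attend, the outcome is measured after the session, and scores within a group are positively correlated. The design is then partially nested in one arm, and an analysis of independent nurses is mildly anti-conservative. Over the assumed ranges the standard error is understated by about 1% to 10%, with type I error of about 5.2% to 7.7%; the middle case gives about 3% and 5.7%. Both drivers, attendance and ICC, are assumptions, and at low attendance with a small ICC the effect is negligible. This is a modest correction to the error bars and to the stated basis of the sample size. It is not evidence that the trial is underpowered.

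**What to change.** - Record an anonymous session-group code for each attendee, linked to the follow-up questionnaire. The article plans nicknames in the sessions and anonymised data, so the link has to be set up deliberately; no personal data are needed.
- State whether follow-up is collected before or after the optional session.
- Analyse CMC and the 26-question score by randomised arm with a partially nested mixed model (a random group effect for attendees only, separate residual variances by arm). Cluster-robust standard errors with a small-sample correction would also do. In both, controls and non-attendees count as clusters of one. If an analysis plan already says this, no change is needed there.
- Add to Sample size that 80% power assumes independent nurses, and give the range under grouping.

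The cost is one code in the data file, a few sentences, a slightly wider confidence interval and a slightly less favourable stated power. No additional participants are needed.
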